## Abstract

The incidence of stroke has increased significantly in recent years. Post-stroke hemiplegia is a common stroke complication with long-term negative consequences. Several studies have suggested that acupuncture could be an effective intervention for the rehabilitation of post-stroke hemiplegia. Intradermal needling is a kind of acupuncture which is widely used in clinical settings. This study attempts to investigate the biomechanical effects of intradermal needle for post-stroke hemiplegia recovery.

This proposed study is a single-centered, prospective, single-blinded (patient-assessor-blinded), randomized clinical pilot trial involving 40 patients with post-stroke hemiplegia. Patients will be randomized to an experimental group or control group in a 1:1 ratio. All of them will receive conventional rehabilitation therapies. Patients in the experimental group will be treated with intradermal needle, whereas patients in the control group will receive sham intradermal needle. The primary outcome measures will be biomechanically validated from the parameters of RSSCAN gait system: plantar pressure distribution, step length, and stride. The scores of clinical scales such as National Institutes of Health Stroke Scale, Fugl-Meyer Assessment, Berg Balance Scale, Barthel Index, and Stroke-specific Quality of Life Scale will be assessed as secondary outcome measures. All assessments will be conducted at baseline, 4 weeks after intervention and at the end of 3 months’ follow-up.

The purpose of this study is to explore the potential effect and biomechanical mechanisms of intradermal needle for post-stroke hemiplegia recovery, as well as to provide a basis for future larger clinical studies.

## Background

1

Stroke has become a leading cause of disability and the second most common cause of death, which amounts to a huge combined burden worldwide.^[1,2]^ In China, there are more than seven million stroke survivors. Approximately, 70% of them are experiencing functional disabilities. Hemiplegia is the most significant symptom.^[3]^ People suffering from hemiplegia face a variety of challenges in regaining independence in daily activities, which not only requires long-term recovery but also increases the burden on the family and society as a whole. It is therefore of great benefit to seek an effective rehabilitation treatment for post-stroke hemiplegia.

Other than the comprehensive rehabilitation techniques, acupuncture is used widely in clinical settings and recommended by the World Health Organization as an alternative and complementary therapy.^[4]^ Many clinical studies about acupuncture for post-stroke hemiplegia have been conducted in the past decades. There is growing evidence confirming that acupuncture can contribute to more patients recovering from akinetic apraxia, regaining muscle strength, improving motor function and returning society.^[5,6]^ Different methods of acupuncture have varying influences. Current acupuncture therapy in common use includes body acupuncture, scalp acupuncture,^[7]^ electro-acupuncture,^[8]^ among others. These kinds of treatment can only stimulate an acupoint temporarily, instead of the full length of time required for the patients’ recovery. Under this context, it is necessary to figure out other methods to extend the time of acupuncture stimulation and enhance the therapeutic effect.

Intradermal needle, a kind of acupuncture, meets the above requirement. This therapy has been developed to treat various diseases because of its distinct advantages in recent years.^[9–12]^ It can be inserted perpendicularly into the skin with a tiny needle and be fixed with a piece of adhesive tape for 1 to 5 days, during which time the patients can move freely without any discomfort. It can provide continuous stimulation to the area, so as to promote effectiveness. To the best of our knowledge, no randomized controlled trials have been performed to demonstrate the clinical curative effect of intradermal needle on post-stroke hemiplegia. In the present study, we will focus on this point and further elucidate it.

In previous work, patients’ motor function and life ability were assessed by scales, which lacks objectivity because the score depends on the researchers partly. Very few studies focused on the objective measure of evaluation.^[13–15]^ The clinical intervention strategies which are used must be backed by a high level of assessment-based support. The RSSCAN gait system can provide biomechanical parameters such as dynamic plantar pressure distribution, step length, foot impulse curve, walking support phase, pace, stride frequency, among others.^[16]^ Because it is a reliable means for foot-examination quantitatively and automatically, it had been used to detect the gait parameters for distinguishing between normal and pathological gait,^[17]^ classifying foot types,^[18]^ even assessing the effect of foot surgery.^[19]^ We mainly use the RSSCAN gait system to evaluate the motor function of lower limb in the present work.

Based on the above, we conceived this clinical pilot trial with the following primary aims. First is to collect preliminary data to observe whether intradermal needle add-on therapy leads to a more effective recovery for patients with post-stroke hemiplegia. Second is to adopt objective outcome measures to elucidate the biomechanical mechanisms underlying the effects.

## Methods/design

2

### Study design

2.1

This study is a prospective, single-centered, randomized, patient-assessor-blinded, parallel-controlled clinical trial. The chief investigator and Clinical Trials Group (CTG) will take responsibility for the overall management of this trial, including the study design, coordination, monitoring, data analysis and results reporting. Any changes to the study protocol will be submitted to them. They will decide whether it is necessary to change or even stop the protocol. We began this study after having discussed in its entirety with each member of the research team. The patients according to inclusive criteria of Dongzhimen Hospital will be recruited and then invited to participate in this study. The eligible participants will be randomly allocated into two groups by a 1:1 ratio using a randomization procedure. All patients will receive conventional rehabilitation therapies. On top of basic treatment, the experimental group will receive authentic intradermal needling, whereas the control group will receive sham intradermal needling. All therapeutic methods will be taken once a day, 5 days per week. This study is designed to coincide with routine care as much as possible and align with follow-up visits. After 4 weeks of treatment and 3-month follow-up, we will evaluate the effects and prognosis by biomechanical indexes from RSSCAN gait system and clinical scales. Our trial design is summarized in Figure 1. The study timeline and event schedule according to the Standard Protocol Items: Recommendations for Interventional Trials (SPIRIT) 2013 Statement^[20]^ are detailed in Figure 2.

**Figure 1 F1:**
[figure not shown]
Flowchart of the study design.

**Figure 2 F2:**
[figure not shown]
Timing of treatment visits and data collection.

### Ethical issues

2.2

Our protocol is in accordance with principles of the Declaration of Helsinki^[21]^ and has been approved by the Research Ethical Committee (REC) of Dongzhimen Hospital, the first affiliated teaching hospital of Beijing University of Chinese Medicine (reference number: ECPJ-BDY-2016–76 ). The protocol has been registered with the Chinese Clinical Trial Registry: ChiCTR-IPR-17011989.

### Sample size

2.3

Out study is a preliminary clinical trial aiming to evaluate the feasibility of intradermal needle therapy for post-stroke hemiplegia recovery. Therefore, we did not determine sample size basing on statistical calculations.^[22]^ An alternative approach to estimate the sample sizes for pilot studies with 10 to 40 patients per group was adopted.^[23]^ Accordingly, to exceed the minimal number and combine with the actual situation, a total of 40 patients will be recruited in this research, 20 in each group. Assuming a 20% drop-out rate, we aimed to recruit 50 patients. Each group will require 25 initial participants.

### Participant recruitment

2.4

Participants will be recruited from Dongzhimen Hospital affiliated with the Beijing University of Traditional Chinese Medicine in Beijing, China. Our study will be promoted via leaflets and through the Internet. We will communicate with prospective participants about study details. If they are interested in participating and willing to sign the informed consent, they will be invited into this study.

### Informed consent

2.5

We will fully explain the details of this study to participants and their families before they take part in this research, including trial objectives, characteristics, probable benefits, potential risks, as well as the obligations as stated in the Declaration of Helsinki *2013*.^[21]^ They will also be informed that their participation in the trial is entirely voluntary and that they can withdraw at any time for any reason. All patients who meet all inclusion criteria and none of exclusion criteria and agree with this trial will give their written informed consents before they undergo any interventions related to this study. Their personal information will be always undisclosed and kept confidential.

### Inclusion criteria

2.6

Participants satisfying the following inclusion criteria will be included: confirmed stroke patients with results from computed tomography or magnetic resonance imaging; aged 35 to 75 years; first-ever stroke or recurrent stroke without neurofunctional disablility (score of modified Rankin Scale ≤2); stable condition after stroke and within 3 months of the duration; with hemiplegia and be able to walk at least 6 m; sufficient cognition to follow commands, Mini-Mental State Examination (MMSE) score >24; never used intradermal needle before; the voluntary informed consent form signed.

### Exclusion criteria

2.7

Participants with any of the following exclusion criteria will be excluded: received thrombolytic therapy or surgery; stroke during 3 months after the onset; stroke without hemiplegia or with but could not walk 6 m; vital signs are not stable or with worsening conditions; with other diseases such as osteoarthrosis that will affect motor function of lower limbs; used intradermal needle before; pregnant or lactating women; participating in other clinical trials.

### Randomization and allocation concealment

2.8

All participants will be assigned to experimental group or control group in a 1:1 ratio according to a computer-generated randomization list by an independent researcher. In accordance with best practice recommendations for randomized controlled trials, allocation concealment will be employed. Assignments will be sealed in opaque envelopes by a nurse who will be trained before the trial and will not participate in treatment. As only the therapist who opens the envelopes will assign patients to a different group. It is impossible to predict and interference the assignments factitiously. The participants will be blinded. They will be told that they have been randomly allocated to one group, and be treated with regular rehabilitation therapies. Moreover, the outcome assessors and data statistical analysts will remain blinded to the intervention methods. Unblinding will be considered when adverse events (AEs) occur.

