### Basic characteristic variables

2.12

We will conduct demographic information of all the participants at baseline assessments, including sex, age, time from the onset of stroke, medical history, clinical syndrome (left or right hemiplegia), diseased location, and other detailed information. Vital signs such as the resting blood pressure, pulse, respiration rate, and body temperature will be measured every day by nurses.

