### Statistical analysis

2.18

Statisticians will be responsible for the statistical analysis. The main analysis will compare the changes in all outcome measurements of between-group or within-group to evaluate the effect of intradermal needle treatment. An intention-to treat analysis will be conducted using the SPSS (Statistical Product and Service Solutions) program (version 22.0, Chicago, IL). Continuous variables will be expressed as means ± standard deviations, Wilcoxon rank sum tests with no adjustment for multiple comparisons will be used for comparisons. Categorical variables will be presented with frequencies or percentages. Fisher exact test will be applied in testing blinding between groups because of small cell counts. A *P* value of <.05 (2-sided) is considered to indicate statistical significance, with 95% confidence intervals.

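### The named between-group test cannot use time from stroke onset, which is already recorded; with about 20 per group this costs precision and leaves chance imbalance uncorrected

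*Protocol article*

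**What the plan says.** **Analysis (section 2.18).** "The main analysis will compare the changes in all outcome measurements of between-group or within-group". For continuous variables, "Wilcoxon rank sum tests with no adjustment for multiple comparisons will be used for comparisons", and a "value of <.05 (2-sided) is considered to indicate statistical significance". The phrase about no adjustment concerns multiplicity, not covariates. The point here is that a rank sum test in its plain form has no place for a covariate or a stratum.

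**Baseline data (section 2.12).** The variables collected include "time from the onset of stroke". No stated analysis uses it.

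**Allocation (section 2.8).** Patients are "assigned to experimental group or control group in a 1:1 ratio according to a computer-generated randomization list by an independent researcher". The article describes neither strata nor blocks, and does not say that there are none.

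**Entry window (sections 2.6 and 2.7).** Inclusion requires "stable condition after stroke and within 3 months of the duration" and the ability to walk 6 m. One exclusion criterion, as worded, is "stroke during 3 months after the onset". The two conflict.

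**Size (section 2.3).** "a total of 40 patients will be recruited in this research, 20 in each group", with 50 recruited to allow for 20% drop-out.

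**Link to outcome (section 2.13).** In support of step length as a primary measure, the article cites a cross-sectional study in which step-length asymmetry was greater in groups at later post-stroke stages.

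**The concern.** Patients at different times after stroke may change by different amounts over the same 4 weeks, whichever needle they receive. Comparing changes removes a difference in starting level. It does not remove a difference in rate of recovery between two patients with the same starting value.

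If time from onset predicts change, two things follow. The variation it causes stays in the error term of every comparison. And when the groups happen to differ in time from onset, that trial's observed difference is shifted, with nothing in the stated analysis to correct it. The trial is meant to supply preliminary effect data for a larger study, and its size is fixed on practical grounds, so using a variable already in hand is the cheapest way to sharpen the estimate.

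**Working it through.** **1. The plan's own figure.** 40 / (1 − 0.20) = 50, or 20 / 0.80 = 25 per group. This reproduces section 2.3. There is no power calculation to check.

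**2. How often the groups differ in time from onset.** Assumptions: half the patients are early after stroke, 20 per group, no stratification. Let X1 and X2 be the numbers of early patients in the two groups. Then X1 − X2 + 20 follows Bin(40, 0.5).
- A gap of 20 points or more means |X1 − X2| ≥ 4: probability 0.268.
- A gap of 30 points or more means |X1 − X2| ≥ 6: probability 0.081.

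**3. What a gap does to the estimate.** Let d be the extra 4-week gain of early over late patients, in within-stratum SDs. The documents give no value; the assumed range is 0.5 to 1.0. A 20-point gap shifts the estimate by 0.20 × d, that is 0.10 to 0.20 SD, in either direction.

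**4. What omission costs in precision.** With half the patients in each class, the between-class variance is d² × 0.5 × 0.5 = d²/4. The variance ratio, unadjusted to adjusted, is 1 + d²/4:
- d = 0.5: 1.0625, about 6% more variance.
- d = 1.0: 1.25, 25% more variance.

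**5. A check under a different model.** 20,000 simulated trials per scenario, 20 per group, normally distributed outcome. Time from onset is assumed uniform over 0 to 90 days (SD 90/√12 = 26 days), with correlation 0.3, 0.5 or 0.7 (in size) with change. The difference in mean onset time has SD 26 × √(2/20) = 8.2 days. It reaches 7 days in 39% of trials, 14 days in 9%, and 0.5 SD (13 days) in 11% (8% with 25 per group).

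| Correlation with change | 0.3 | 0.5 | 0.7 |
|---|---|---|---|
| Shift at 0.5 SD imbalance (outcome SD) | 0.15 | 0.25 | 0.35 |
| False positives, Wilcoxon, all trials | 4.9% | 5.0% | 4.7% |
| False positives, Wilcoxon, imbalance ≥ 0.5 SD | 8.1% | 14.2% | 21.0% |
| False positives, onset-adjusted linear model, imbalance ≥ 0.5 SD | 5.1% | 4.9% | 4.3% |
| Power for an assumed 0.8 SD effect, Wilcoxon | 67% | 67% | 65% |
| Power for the same effect, adjusted | 72% | 80% | 93% |

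Two cautions on this table. The range of d in steps 3 and 4 corresponds to correlations (d/2)/√(1 + d²/4) of 0.24 to 0.45, so the 0.7 column lies well outside it. And part of the power gain comes from replacing a rank test with a linear model on normal data; that part is small, about 2 points by a normal approximation (0.716 against 0.696).

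**The case against.** Much of the case on the other side stands.

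- **Allocation.** A reader might infer that the list is unstratified. The article does not say so, and a condensed article commonly leaves strata and blocks to the full protocol. The point therefore rests on the test named in section 2.18, not on section 2.8. An adjusted supplementary analysis may also exist in a plan that is not shown.
- **Bias.** A reader might infer that onset time biases the trial toward a needle effect. Randomisation rules this out on average: the false-positive rate over all trials is about 5%. The excess appears only conditional on an unlucky draw, as with any prognostic factor in a small trial.
- **Speed of recovery.** A reader might supply the premise that recovery is changing rapidly at entry. The document does not state it. The study cited in section 2.13 is cross-sectional and concerns the level of symmetry, not change over 4 weeks. It makes onset time a reasonable candidate covariate and gives no effect size.
- **Entry at any time up to 3 months.** This follows from section 2.6 alone. Section 2.7, read literally, says something else, and the 6 m walking requirement may remove some very early patients.
- **Size.** The standard error at 20 per group is √(2/20) = 0.32 SD. A shift of 0.10 to 0.20 SD is about one third to just under two thirds of that, in a declared pilot. Other covariates could also be proposed.

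What the objection does not remove is that the plan names a comparison unable to use a variable it collects, when adjustment costs almost nothing.

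**Conclusion.** The point holds as one of efficiency and of robustness to chance imbalance. The stated comparison in section 2.18 leaves out time from onset. If that variable predicts 4-week change by 0.5 to 1.0 SD between early and late patients, the variance of the contrast is about 6% to 25% larger than it need be. A 20-point imbalance, with probability 0.27 under the half-early assumption, shifts that trial's estimate by 0.10 to 0.20 SD in either direction. If onset time does not predict change, almost nothing is lost either way.

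The early share, the value of d and the correlations are all assumptions; the documents supply none of them. The documents do not support a claim of systematic bias, of inflated overall type I error, or of a list known to be unstratified.

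**What to change.** In section 2.18, before unblinding, do one of the following for the between-group comparison:

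1. Pre-specify a model (linear or rank-based) with group, the baseline value of the outcome and time from onset; or
2. Keep the rank sum test and stratify it by time from onset, at a cut fixed before unblinding. This is simpler but uses less of the information in onset time.

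Report time from onset by group in either case. Before any cut is chosen, the entry windows in sections 2.6 and 2.7 must be reconciled, because they determine what range of onset times the trial contains.

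The cost is wording and one degree of freedom for onset time: with 40 patients, 38 residual degrees of freedom become 37, or 36 with the baseline value as well. No extra data, visits or patients are needed.

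Changing the allocation list to strata and blocks for the remaining patients is not recommended. Enrolment is under way (section 3.1) and the therapist opens the envelopes (section 2.8), so small blocked strata would make assignments easier to predict. The analysis change obtains the benefit without that risk.

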### Interventions and comparison

2.9

#### Experimental group

2.9.1

Patients allocated to the group will receive conventional rehabilitation programs as control group. As the aim of our study is to analyze the effects of intradermal needle for stroke hemiplegia recovery, participants in this group will be treated by intradermal needle-embedding in addition. The appearance of intradermal needle is in Figure 3. According to a summary of previous investigation^[24–26]^ and clinical experience, taking into account the patients’ normal activities while avoiding contact with shoes and socks, we selected following acupoints from the affected side for needling: Liangqiu (ST34), Yanglingquan (GB34), Yinlingquan (SP9), Xuanzhong (GB39), Fuyang(BL59), Sanyinjiao (SP6). The intradermal needle will complies with the Standardize Manipulations Of Acupuncture And Moxibustion-Part 8: Intradermal Needle (GB/T 21709.8–2008).^[27]^ All acupoints are located according to the World Health Organization standard acupuncture point locations.^[28]^

**Figure 3 F3:**
[figure not shown]
Intradermal needles (sham: left, authentic: right).

The intradermal needles (0.2 × 1.5 mm, Seirin, Japan) (Fig. 2) are disposable and sterile, with waterproof adhesive tape above which can help to affix the needle beneath. Patients after modern rehabilitation training will be inserted with these needles in a perpendicular fashion. In comparison to typical traditional acupuncture, intradermal needles are smaller, less deeply, and with less manipulation. All needles will be replaced after treatment the next day. In other words, patients will carry these intradermal needles for the whole course of therapy. The intradermal needle treatment will be implemented once a day from Monday to Friday, lasting 4 weeks. To ensure the optimal effects of needle stimulation, our therapists will be required to have clinical experience of acupuncture treatments for at least 8 years. The items are presented in the Standards for Reporting Interventions in Clinical Trials of Acupuncture (STRICTA).^[29]^

#### Control group

2.9.2

Patients allocated to the control group will receive conventional rehabilitation programs for post-stroke hemiplegia. Therapies are based on neurodevelopmental theory and will include position of limb, passive and active assisted activities, postural balance training, trunk controlling, task oriented practicing, among others.^[30]^ It will last approximately 1 hour every time. After this treatment, sham intradermal needles, which look similar at the surface but without needle underneath will be used. It can be adhered to the skin instead of being needle-inserted. The acupoints location and manipulations are taken equally with experimental group. The retention time and frequency are identical to authentic intradermal needle therapy. To ensure the homogeneity of research, all rehabilitation programs will be done by qualified therapists and we have trained them with rehabilitation technology before the implementation of the project (Fig. 1).

